3) *Surrogate outcomes.* CPAP treatment for those with severe OSAS is largely offered for symptomatic relief, and until the results of current RCTs are available, it is unknown whether this treatment can prevent stroke, myocardial infarction or cardiovascular death. Repeated retinal imaging of those with heavy snoring and OSAS, treated with CPAP, may demonstrate reversal of retinal microvascular signs. These data will improve our understanding on how snoring and OSAS confer excess vascular risk, and strengthen the indications for CPAP therapy to reduce vascular risk.

***Only one published study has addressed the issue of retinal microvascular abnormalities in OSAS (6).*** The Sleep Heart Health Study examined 2,927 subjects, but only 1% of subjects had a clinical diagnosis of OSAS. Thus the study was underpowered to detect retinal abnormalities as a function of OSAS. Nevertheless, the overall prevalence of retinopathy was increased at higher AHI values, and an increase in AHI from 0 to 10 was associated with a decrease in the arteriole-to-venule ratio (AVR). The authors concluded that further investigation was warranted.

Preliminary analysis of data from the **Blue Mountains Eye Study** (BMES; CIC) demonstrated a large increase in venular calibre for a self reported history of OSAS (224.5µm) versus non affected non-snorers (219.7 µm; p=0.06), suggestive of early microvascular disease. Data from the **Wisconsin Sleep Cohort** (n=491) have demonstrated that a higher AHI was positively associated with wider retinal venular calibre (for AHI >15 events/hour, OR 2.08 [1.03-2.16]; p<0.05), independent of other cardiovascular risk factors (personal communication). This supports an association of SDB with microvascular mediated cerebrovascular disease.

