**Statistical Analysis and Sample Size:** Univariate relationships between measures of OSAS or snoring severity (AHI, Arousal Index, Oxygen Desaturation Index, snore index) [independent variables], and overnight change in CRAE, CRVE, AVR and IMT [dependent variables], will be examined using linear regression analysis for continuous data and  $X^2$  analysis for categorical data. Stepwise multiple linear regression or logistic regression will be used to examine associations of OSAS and snoring (continuous data) with dependent variables, including any interactions with anthropometric and vascular risk factor data. From our preliminary data, a sample size of 384 for the cohort study will have 80% power to detect a difference in the CRVE means of 8.0  $\mu\text{m}$  (and difference in CRAE means of 13.6  $\mu\text{m}$ ), assuming that the common standard deviation is 24.1  $\mu\text{m}$  for CRVE and 13.6  $\mu\text{m}$  for CRAE, using a two group t-test with two sided significance of  $p=0.017$ . For the overnight changes, a sample size of 146 will have 80% power to detect a correlation coefficient of 0.25 between AVR and snoring using linear regression, assuming normal distribution of AVR and a two sided significance level of  $p=0.025$ . Power estimates are conservative based on the dependent variables with the smallest detected signals from our preliminary retinal data.

**Outcomes:** This study will establish the relationship between snoring / OSAS and the presence of cerebral microvascular and macrovascular disease in a cross section of subjects. Overnight changes in the retinal vessel calibre will demonstrate for the first time a mechanism by which SDB acutely and adversely affects the microvasculature. In addition, if the cross-sectional analysis of subjects

demonstrates the same changes in vessels as a function of SDB severity, then this would support these changes becoming chronic over time. Finally, we will examine for the presence of retinal emboli before and after sleep, which will provide the first evidence for snoring and OSAS being associated with active plaque disease, with potential for plaque disruption and embolic stroke.

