**Overnight CPAP review studies using the patient's CPAP treatment pressure will be undertaken at 6 months and one year.** Repeat carotid Doppler ultrasound (pm), retinal photography (pm and am), blood pressure (pm and am), fasting blood lipids and sugar, and weight will be measured.

**This duration of study is adequate to detect clinically relevant outcomes.** An increase in IMT of >0.03 mm/year is detectable and clinically relevant, as it is associated with a doubling in incidence of coronary events (44). We anticipate a reduction of at least this amount (15). For retinal photography, a decrease in 3.5  $\mu$ m/year of arteriolar calibre is detectable, measurable in a one year time frame, and associated with a 10 mmHg increase in mean arterial blood pressure (31), making it clinically relevant. Both arteriolar narrowing and venular widening are predictive of stroke (59).

**We have chosen to compare the same subjects before vs after the intervention but not to have an untreated control arm in this study** due to efficiency of paired comparison and the well recognised ethical problems with not treating severe OSAS. This will enable a valid paired comparison with the differences between the before and after treatment measures being related to the treatment intervention over 1 year. The primary outcome variables (CRAE, CRVE, AVR and IMT) are objective measures of structural changes which are unlikely to spontaneously improve without intervention, or be affected by a placebo type response.

***We acknowledge that compliance with CPAP treatment will be a critical factor to the success of this trial.*** Patients will be offered as much support as required in the initial phases of the trial by the study co-ordinator, with four weekly review throughout the study. Patients will be able to contact the study co-ordinator at any time to resolve problems. CPAP compliance will be monitored objectively by nights and hours of use from machine downloads at study visits, together with compliance with routine medication(s). We will target a minimum compliance of 4 hours per night.

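### Project 1 sample size: the CRAE difference said to be detectable with 80% power (13.6 µm) repeats the SD; the stated inputs give about 4.5 µm, and the claim of conservatism should cover only the overnight correlation

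*Protocol*

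**What the plan says.** The relevant text is in the protocol, Project 1, Statistical Analysis and Sample Size. It states that "a sample size of 384 for the cohort study will have 80% power" for a between-group comparison of retinal vessel calibre. Two detectable differences are given: "a difference in the CRVE means of 8.0" µm, and in brackets "and difference in CRAE means of 13.6" µm. The standard deviations follow directly, "assuming that the common standard deviation is 24.1" µm for CRVE and 13.6 µm for CRAE. The test is a two-group t-test at a two-sided level of 0.017. The allocation between the groups is not stated.

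A second calculation in the same paragraph covers the overnight changes: 146 subjects for a correlation of 0.25 between AVR and snoring at a two-sided level of 0.025.

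The paragraph closes with a statement that covers both calculations: "Power estimates are conservative based on the dependent variables with the smallest detected signals from our preliminary retinal data".

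Two other places bear on that statement. The Background, under the roles of retinal imaging, reports that the population eye study "demonstrated a large increase in venular calibre for a self reported history of OSAS", 224.5 µm against 219.7 µm in unaffected non-snorers (p=0.06). The Preliminary Data section reports pilot correlations of 0.42 (snoring time with arteriolar narrowing; 0.38 in the caption to Figure 2) and 0.38 (oxygen desaturation with falling AVR).

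**The concern.** The CRAE difference and the CRAE SD are the same number, a standardised difference of 1.0. The CRVE difference beside it is 8.0/24.1 = 0.33 SD. One sample size, one alpha and one test cannot give 80% power for both.

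This paragraph is the protocol's statement of what the Project 1 group comparison can detect. As written, it tells the reader that arteriolar differences below 13.6 µm are out of reach, which understates the design's sensitivity about threefold. The claim of conservatism can mislead in the other direction. It invites the reader to treat 8.0 µm as a cautious venular assumption, although the document gives no source for that figure and the one comparable difference it does report is smaller.

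**Working it through.** **Inputs** (Project 1, Statistical Analysis and Sample Size): N = 384; power 80%; two-sided alpha 0.017; CRVE difference 8.0 µm with SD 24.1 µm; CRAE difference 13.6 µm with SD 13.6 µm. Assumption: 1:1 allocation, 192 per group.

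**Formulas.** Normal approximation: n per group = 2 × (z₁ + z₂)² × (SD/difference)², and detectable difference = (z₁ + z₂) × SD × √(1/n₁ + 1/n₂). Here z₁ = 2.387 (two-sided 0.017) and z₂ = 0.842 (80% power), so the sum is 3.228 and its square 10.42. Results were checked with the exact noncentral t.

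**Step 1: reproduce the CRVE figure.**
- n = 2 × 10.42 × (24.1/8.0)² = 189.2, so 190 per group; 191 by exact t, or 382 in total against 384 stated.
- Power at 192 per group: 80.3% (exact t).

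The CRVE half reproduces, which supports the reading of test, alpha and 1:1 split.

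**Step 2: test the CRAE figure on the same inputs.**
- n = 2 × 10.42 × (13.6/13.6)² = 20.8, so 21 per group; 23 per group by exact t (81.4% power; 22 per group gives 79.3%).
- Power at 192 per group for 13.6 µm: above 99.9%.

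The CRAE half does not reproduce.

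**Step 3: the CRAE difference that the inputs give.**
- 3.228 × 13.6 × √(2/192) = 3.228 × 13.6 × 0.1021 = 4.48 µm; exact t 4.50 µm.
- Cross-check by the CRVE standardised effect: 0.332 × 13.6 = 4.51 µm.

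**Step 4: could another reading give 13.6 µm?** Detectable CRAE difference at 80% power:

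| Variant | µm |
|---|---|
| 192 v 192, alpha 0.05 | 3.9 |
| 192 v 192, alpha 0.025 | 4.3 |
| 384 per group, alpha 0.017 | 3.2 |
| 128 v 128, alpha 0.017 | 5.5 |
| 119 v 265 (31% v 69% of 384), alpha 0.017 | 4.9 |
| 164 v 121 (42% v 31% of 390), alpha 0.017 | 5.3 |
| 27 v 357 (7% v 93% of 384), alpha 0.017 | 8.8 |

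The percentages are the laboratory's referral mix in the Subjects paragraph (RDI <5 in 7%, 5-15 in 24%, >30 in 42%). None of these gives 13.6 µm. A split of about 11 v 373 would, but it is incompatible with the CRVE figure: even at 27 v 357, power for 8.0 µm is 23%.

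**Step 5: is 8.0 µm conservative?**
- Between-group CRVE difference in the Background: 224.5 − 219.7 = 4.8 µm. The planning value is 8.0/4.8 = 1.67 times that.
- Power for 4.8 µm at 192 v 192: 33%. For 80% power: 527 per group (exact t).
- Overnight calculation: planned 0.25, pilot 0.38 to 0.42. The planning value is below the observed ones.

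**The case against.** - **The slip has little consequence.** This stands. CRVE sets the sample size and reproduces, so neither N nor conduct changes, and the error makes the design look weaker than it is. The figure is still wrong as stated.
- **The claim of conservatism is partly right.** This stands too. It directly follows the overnight calculation, which plans for a smaller correlation than the pilot showed. Neither pilot correlation is for AVR with snoring itself, but both exceed 0.25. Deleting the sentence outright would go too far.
- **The 4.8 µm is a different contrast.** It compares self-reported OSAS with non-snorers in a population sample. Project 1 compares severe with control/mild cases classified by sleep study in a referral clinic, and self-report may dilute the difference. A reader might infer that 8.0 µm is wrong, or that the venular comparison is underpowered. The documents do not show that. They show only that 8.0 µm has no stated source and exceeds the one comparable figure. Nor is that figure the only cross-sectional evidence: the Background also gives an odds ratio for wider venules and a lower AVR with rising AHI. It is the only between-group venular difference in µm.
- **A relevance threshold of 3.5 µm.** A reader might set the 4.5 µm against the Project 2 text beginning "For retinal photography, a decrease in 3.5" µm per year and conclude that Project 1 is too small for its own arteriolar threshold. The protocol does not make that transfer. The 3.5 µm is a yearly within-patient change used to defend the 12-month duration of Project 2, not a between-group target for Project 1.
- **Group sizes.** The 1:1 split is not stated. The 164 v 121 split applies the referral mix, whereas the protocol plans recruitment stratified across the severity range without giving proportions. It is only an illustration.
- **The regression analyses.** The planned multivariable models treat snoring and OSAS as continuous. The power figures here describe only the two-group t-test on which the protocol bases its sample size.

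**Conclusion.** The CRAE figure is wrong as written. From the stated SD, alpha and total, with 1:1 allocation assumed, 80% power corresponds to 4.5 µm, not 13.6 µm: a factor of about three. Under 164 v 121 it would be about 5.3 µm. That the SD was copied into the place of the difference is an inference, though a strong one; that 13.6 µm does not follow from the inputs is arithmetic. The sample size of 384 stands on the CRVE calculation.

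The claim of conservatism holds for the overnight correlation and is unsupported for the group comparison. If the true CRVE difference were the 4.8 µm in the population data, power at 192 v 192 would be about 33%. That is conditional on a benchmark that may understate the clinic contrast, so it is a reason to give a source for 8.0 µm or to limit the claim. It is not proof that the study is too small.

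**What to change.** In Project 1, Statistical Analysis and Sample Size:

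1. Replace the CRAE difference of 13.6 µm with 4.5 µm, and state that both detectable differences assume two equal groups of 192.
2. Restrict the statement that the power estimates are conservative to the overnight correlation calculation. If the investigators have a source for the 8.0 µm CRVE difference, cite it there.

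The cost is one figure, one added assumption and one narrowed sentence. Sample size, recruitment and conduct are unchanged.

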## RESEARCH PLAN:

### PROJECT 1: The Influence of Untreated Snoring and OSAS on Cerebral Vascular Disease.

**Hypotheses:** 1) Patients with untreated heavy snoring and OSAS will demonstrate an increased prevalence of retinal microvascular and carotid macrovascular abnormalities.

2) Microvascular and macrovascular abnormalities will increase over a night of sleep, with the overnight increase correlating with the severity of the snoring and OSAS.

3) Patients with untreated heavy snoring and OSAS, and with established carotid atherosclerotic plaque, will demonstrate an increased incidence of overnight retinal arteriolar emboli (compared with normal controls), consistent with active carotid plaque disease.

**We propose to address the above hypotheses by comparing pre and post sleep data in patients with untreated heavy snoring and OSAS and comparing any differences to those with mild or no snoring and OSAS, to directly address the following specific research questions:**

- 1) Do patients with heavy snoring and OSAS demonstrate an increased baseline prevalence of microvascular disease (retinal vessel changes) and/or macrovascular disease (carotid artery IMT)?
- 2) Do patients with OSAS demonstrate a decrease in arteriolar diameter or an increase in retinal venular diameter following overnight sleep as a function of the severity of their OSAS or snoring?
- 3) Do patients with heavy snoring and OSAS, and with carotid atherosclerotic plaque, demonstrate a higher frequency of prevalent and overnight incident retinal arteriolar emboli?

**Design:** Nested case-control cohort study in snoring and OSAS referrals, comparing severe cases with control/mild cases (see below) at baseline and for overnight changes in vascular abnormalities.

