*Retinal Photography:* Each eye will be photographed following a standardized protocol using a high-resolution digital camera (Canon non-mydratic). Two colour retinal photographs will be taken from each eye, one centred on the optic disc (Diabetic Retinopathy Study [DRS] standard field 1) and another on the macula (DRS standard field 2) (13). Digital images will be graded for retinal microvascular lesions using standard protocols under direction of CIC. Qualitative signs will be recorded (see Background p3). The intra-grader reliability for detecting focal arteriolar narrowing and AV nicking is (kappa statistic) 0.80 and 0.87, respectively (57).

A computer-assisted grading method with high reproducibility will be used to measure the retinal vessel diameters and arteriole-to-venule ratio (AVR). Average retinal arteriolar or venular width (diameter) is calculated using the Parr-Hubbard formula (23, 45) and presented as the central retinal arteriolar equivalent (CRAE) or central retinal venular equivalent (CRVE). AVR can then be calculated from CRAE and CRVE. Intra- and inter-grader reliability of this method is high (51). Retinal emboli are intravascular lesions seen along the course of retinal arterioles, and may be present at a bifurcation. Detailed methods of grading retinal abnormalities have been described (57).

**Protocol:** Subjects will undergo an overnight PSG study. Carotid ultrasound, retinal photography and supine blood pressure will be performed at ~2000hrs and repeated at ~0600hrs. A major outcome focuses on overnight change in measurements, where subjects act as their own controls.

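### Project 1's baseline vessel comparison is planned at a flat p=0.017; Holm's step-down on the same three tests would keep the 5% error and could add power at no cost in patients (optional gain, not an error)

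*Protocol*

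**What the plan says.** All of this is in the protocol under Project 1. The Design paragraph describes a baseline contrast "comparing severe cases with control/mild cases", so moderate cases fall in neither group. The Statistical Analysis and Sample Size paragraph states that "a sample size of 384 for the cohort study will have 80% power" "to detect a difference in the CRVE means of 8.0" µm in CRVE, "assuming that the common standard deviation is 24.1" µm. It also gives a "difference in CRAE means of 13.6" µm, which equals the CRAE standard deviation printed in the same sentence. The test is specified "using a two group t-test with two sided significance of $p=0.017".

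That is the only place where 0.017 appears. The next sentence, on overnight change, uses a two-sided level of 0.025. No sentence says which three tests share the 5% error, or which procedure will be used to test them. The Retinal Photography paragraph adds that "AVR can then be calculated from CRAE and CRVE".

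**The concern.** The level 0.017 is 0.05/3 to three decimals, which is a Bonferroni split over three tests. Bonferroni holds every test to the strictest level, even after other tests in the family have been rejected. Holm's procedure compares the smallest p-value with 0.05/3, the next with 0.025 and the last with 0.05, stopping at the first failure. It controls the same family-wise error, and it rejects everything that Bonferroni rejects and sometimes more.

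The difference could matter here because the vessel measures are linked. The study expects arterioles to narrow and venules to widen, and both changes lower AVR. If AVR belongs to the family, it is likely to be rejected first, so CRVE and CRAE could be tested at 0.025 and 0.05. A flat rule would still hold them to 0.017. What is at stake is power on arteriolar and venular diameter; the false-positive rate is not affected.

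**Working it through.** **Inputs.** From the Project 1 sample-size paragraph: CRVE difference 8.0 µm with SD 24.1 µm, CRAE SD 13.6 µm, total N 384, power 80%, two-sided 0.017. From the Subjects paragraph: 390 patients; referral shares of 7% normal, 24% mild, 27% moderate and 42% severe. From the Preliminary Data: evening CRAE 153.9 ± 13.5, CRVE 222.9 ± 23.2, AVR 0.69 ± 0.06.

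**1. The plan's own figure.** n per group = 2(z₁₋α/₂ + z₀.₈₀)² SD²/Δ². With α = 0.05/3: 2 × (2.394 + 0.842)² × 24.1²/8.0² ≈ 190, rounded up to 191. The noncentral t gives 192 per group, 384 in total, which is the printed number. With α = 0.017 exactly, the t-based total is 382. So 384 reproduces as two equal groups at 0.05/3.

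**2. The CRAE difference.** With 192 per group, the difference detected with 80% power is 13.6 × (2.387 + 0.842) × √(2/192) ≈ 4.5 µm. The printed 13.6 µm would need only about 21 per group. The value 4.5 µm is used below as an assumption.

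**3. Floor and ceiling for CRVE power at 8.0 µm (noncentral t).** Under Holm, CRVE is tested at 0.05/3, 0.025 or 0.05, depending on the other two results.

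| Groups | at 0.05/3 | at 0.025 | at 0.05 |
|---|---|---|---|
| 192 v 192 | 80.1% | 84.1% | 90.0% |
| 164 v 121 | 64.1% | 69.7% | 78.8% |

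The second row assumes that the referral mix carries over: 42% of 390 = 164 severe; 7% + 24% = 31% of 390 = 121 control/mild.

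**4. Correlation of CRAE and CRVE.** By the delta method, CV²(AVR) ≈ CV²(CRAE) + CV²(CRVE) − 2ρ·CV(CRAE)·CV(CRVE). The CVs are 13.5/153.9 = 0.0877, 23.2/222.9 = 0.1041 and 0.06/0.69 = 0.0870. So ρ = (0.00769 + 0.01083 − 0.00756)/(2 × 0.0877 × 0.1041) ≈ 0.60. Rounding of the AVR SD (0.055 to 0.065) gives a range of 0.53 to 0.67.

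**5. Simulation, with AVR computed as the ratio and taken as the third test (ρ = 0.6).** CRVE power, flat 0.05/3 against Holm:

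| Scenario | 192 v 192 | 164 v 121 |
|---|---|---|
| Only venules change (8.0 µm) | 80% → 84% | 64% → 68% |
| Arterioles also narrow by 4.5 µm | 80% → 89% | 64% → 77% |

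Separate runs differ by about one point. In the second scenario, the chance of rejecting all three rises from about 60% to 80% (192 v 192) and from 33% to 58% (164 v 121). With arteriolar narrowing of 2.2 µm and 164 v 121, one run gave 64% → 72%. With no true difference anywhere, the family-wise error was about 4.5%.

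**6. If the third test is not AVR.** With 161 v 119 (42% and 31% of 384), a third outcome with no effect, correlations of 0 to 0.5 and a CRAE effect of 4.5 µm, CRVE power goes from 64% to about 67%. If both other outcomes are null, it stays at 64%.

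**The case against.** The strongest reply is that nothing here is wrong. The level 0.017 is a planning assumption in one sentence, sizing at 0.05/3 is compatible with a later Holm analysis, and the testing procedure may be set in a statistical analysis plan that is not shown. All of that stands, and it limits the point to a suggestion.

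Several stronger readings are tempting but are not supported:

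- A reader might infer that 0.017 governs every Project 1 comparison. It does not; the overnight correlation is planned at 0.025.
- A reader might take the family to be CRAE, CRVE and AVR. The protocol does not say so. The sentence names only CRVE and CRAE, and the background calls IMT the primary macrovascular outcome, so IMT is a plausible third member. The argument that AVR is rejected first would then fall away.
- A reader might state the gain as 64% to 78% in the groups actually compared. Recruitment is to be stratified by severity and no group sizes are given, so 164 v 121 is an assumption. A figure near 78% is close to the power of a single test at 0.05, and needs the other two tests to be rejected almost every time.
- A reader might blame the flat level for the fall from 80% to 64%. That fall comes from sizing two equal halves of 384 while leaving moderate cases out of the contrast. Under the referral-mix split, even Holm's ceiling (78.8%) stays below 80%.

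Holm also has a small price. Bonferroni comes with simple simultaneous confidence intervals that match its tests, and Holm does not.

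**Conclusion.** The point holds as an optional efficiency gain. The planning level matches a flat three-way split. That split is valid, but Holm on the same three tests is never less powerful and controls the same error, whichever three outcomes form the family.

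The size depends on what is assumed. With AVR as the third test, the gain in CRVE power is about 4 points if only venules change. If arterioles also narrow by 4.5 µm, it is about 9 points at 192 v 192 and about 13 at 164 v 121. If the third outcome is unrelated and null, it is about 3 to 4 points at 161 v 119, and almost nothing if both other outcomes are null. The 4.5 µm difference, the correlation of 0.6, the make-up of the family and the unequal split are all assumptions.

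**What to change.** In the Project 1 Statistical Analysis and Sample Size paragraph, name the three baseline comparisons that share the 5% error. State that they are tested by Holm's step-down: smallest p-value against 0.05/3, next against 0.025, last against 0.05, stopping at the first that fails. Keep 0.017 as the sample-size level, so that for any given group sizes the power calculated at that level is in effect a floor. Report Bonferroni or unadjusted confidence intervals alongside, labelled as such.

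The cost is one or two sentences, written before the data are seen, and the loss of simple simultaneous intervals that match the tests. No patients, measurements or error control are given up. The sizes of the two compared groups and the printed CRAE difference need separate attention; this change does not settle either.
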